**Methods and design:**

The Liraglutide to Improve corONary haemodynamics during Exercise streSS (LIONESS) trial is an investigator-initiated single-centre randomised double-blinded placebo-controlled crossover proof-of-principle physiological study. Primary endpoints are change in rate pressure product at 0.1 mV ST-segment depression and change in degree of ST-segment depression at peak exercise during sequential exercise tolerance testing performed over a 6-week study period in which 26 patients will be randomised to either liraglutide or saline with crossover to the opposing regimen at week 3.

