**Table 2 Tab2:** **Primary outcome measures**

•	Change in rate pressure product at 0.1 mV ST-segment depression during sequential exercise tolerance testing performed over a 6-week study period
•	Change in degree of ST-segment depression at peak exercise during sequential exercise tolerance testing performed over a 6-week study period

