### Sample size calculation

The host department has shown that the time taken to 0.1 mV STD (368 ± 34 → 418 ± 36 seconds) and the rate pressure product at 0.1 mV STD (20500 ± 755 → 21907 ± 764 mmHg/min) is significantly increased during the second of two serial exercise tests separated by 15 minutes in chronic CAD patients with known left anterior descending artery stenoses [47,48]. This effect is attributed to warm-up angina, which is thought to augment the innate resistance of the myocardium to an ischaemic insult [51,52]. We would expect the administration of Liraglutide to mimic the beneficial cardioprotective effects of warm-up angina. A sample size of 26 patients randomised in a 1:1 fashion to each treatment arm (taking into consideration a >10% drop-out rate) followed by crossover would have 90% power to detect a difference between the means of approximately 15% (2-sided α = 0.05).

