### Data management and analysis

Data will be collected prospectively using a customised paper Case Report Form (CRF). Investigators will record adverse events, injection site reactions, angina episodes and clinical and laboratory parameters on the CRF at each study visit.

The fundamental principle underpinning the design of this trial is that the 2-week period between the Week 3 ETT and the Week 5 ETT (see Figure 1), in those patients randomised to the active liraglutide intervention first, should be sufficient to allow adequate washout of the drug and therefore minimise the impact of a potential carryover effect. Given that the half-life of liraglutide is 10–14 hours, this 2-week washout period far exceeds the generally accepted mark of ≥5 half-lives. A washout period for those randomised to the placebo arm first would not apply per se. A preliminary test, such as the Wilcoxon rank sum test, will be applied to ensure there is no carryover effect. Once this has been established, standard two-sample t-tests for independent samples using the intra-individual differences between the outcomes in both study periods as the raw data will be utilised [53].

A multiple regression model will be used to compare treatment, visit number, and patient, using least squares. Linear regression will be used to study the correlation between outcome parameters and baseline patient characteristics. A p value <0.05 will be considered statistically significant.

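### Two unranked primary endpoints share one unadjusted 0.05 threshold: if either suffices, the false-positive chance is up to 9.75%; if both are required, the stated 90% power does not describe trial success

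*Protocol article*

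**What the plan says.** The abstract (Methods and design) uses the plural: "Primary endpoints are change in rate pressure product at 0.1 mV ST-segment depression and change in degree of ST-segment depression at peak exercise". Table 2 lists the same two measures, "Change in rate pressure product at 0.1 mV ST-segment depression during sequential exercise tolerance testing performed over a 6-week study period" and "Change in degree of ST-segment depression at peak exercise during sequential exercise tolerance testing performed over a 6-week study period", with no order between them.

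The section on data management and analysis closes with one general criterion: "A p value <0.05 will be considered statistically significant". It makes no distinction between the two primaries, the secondary outcomes in Table 3 and the regressions on baseline characteristics.

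The sample size section starts from "A sample size of 26 patients randomised in a 1:1 fashion to each treatment arm", allows for attrition ("taking into consideration a >10% drop-out rate"), and says that this "would have 90% power to detect a difference between the means of approximately 15% (2-sided α = 0.05"). It does not say which endpoint the 90% refers to.

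**The concern.** The number of primary endpoints, the rule for calling the trial positive, and the alpha behind the sample size have to fit together. Here there are two primaries, one unadjusted threshold and one power statement at a single 0.05.

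Under either simple reading, one of the stated figures needs qualifying. If a significant result on one endpoint is enough, two tests at 0.05 give a familywise error above 5%. If both must be significant, the error is controlled, but 90% for one endpoint is not the probability that the trial succeeds. The 5% and the 90% hold together only with a single named primary or an ordered test, and the article has neither. At stake is the error rate behind a claim that liraglutide improves exercise haemodynamics when only one of the two primaries is significant.

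**Working it through.** **Inputs**
- Two primary endpoints (abstract; Table 2).
- Threshold 0.05 (data management and analysis).
- N = 26, drop-out above 10%, power 90%, two-sided alpha 0.05, difference about 15% (sample size calculation). Evaluable patients: 26 × 0.9 = 23.4, taken as 23.
- Correlation between the endpoints: not given. It is assumed here and varied from 0 to 0.9. Both endpoints come from the same exercise tests in the same patients, so some correlation is plausible. For two-sided tests only its absolute size matters.

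**1. The plan's own figure.** The 90% cannot be reproduced, because the article gives no SD of the within-patient difference and does not label its ± values. With 23 evaluable patients, 90% power for a 15% difference would need an SD of the difference of about 21% of the mean (t-test). What follows therefore takes 90% at 0.05 as given. That is an assumption and has not been verified.

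**2. Either endpoint suffices.** Under independence, the chance of at least one false positive is 1 − (1 − 0.05)² = 1 − 0.9025 = 9.75%. For correlated endpoints it is 1 − P(|Z1| < 1.96 and |Z2| < 1.96), with Z1 and Z2 bivariate normal:

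| Assumed correlation | Chance of at least one false positive |
|---|---|
| 0 | 9.75% |
| 0.3 | 9.5% |
| 0.5 | 9.1% |
| 0.7 | 8.35% |
| 0.8 | 7.8% |
| 0.9 | 7.0% |

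Simulating the planned two-sample t-tests on period differences, with 12 or 13 patients per sequence, gives 9.6–9.8%, 9.0–9.1% and 7.9% at correlations 0, 0.5 and 0.8. The small sample does not change the picture.

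**3. Both endpoints required.** The chance that both tests reject cannot exceed the chance that a truly null one rejects, so it is at most 5%. Joint power with 90% per endpoint under independence is 0.90 × 0.90 = 81%.

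**4. Effect of adjusting.** Testing each endpoint at 0.025 gives a familywise error of 1 − 0.975² = 4.94% under independence and 4.65% at correlation 0.5.
- Power for one endpoint, normal approximation: Φ(1.960 + 1.282 − 2.241) = Φ(1.00) = 84%. With the t-test and 22–26 evaluable patients it is about 83%.
- Holm tests the smaller p-value at 0.025 and, if that is significant, the larger at 0.05. Power for a given endpoint therefore lies between this figure and 90%.
- Restoring 90% at 0.025 multiplies N by ((2.241 + 1.282)/(1.960 + 1.282))² = 1.18. Then 26 × 1.18 = 30.7, so 31. From 23 evaluable, 23 × 1.18 = 27.1, so 28, and 28/0.9 = 31.1, so 32 enrolled.

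**The case against.** **It may sit in an unseen analysis plan.** The article is condensed, and multiplicity rules are commonly left to a statistical analysis plan. That disposes of any complaint that detail is absent. It does not dispose of this point, which rests on what the article does state: two primaries, one unadjusted threshold, and one alpha behind the sample size.

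**The study is small and exploratory in spirit.** It is a single-centre proof-of-principle trial. Both primaries are prespecified, and the sponsor commits to reporting positive or negative results, so a reader who sees both p-values can weigh them. This stands and lowers the severity. It does not remove the mismatch, since the article itself invokes 90% power and a significance threshold.

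**Stronger readings that the documents do not support.**
- A reader might infer that the plan has a false-positive rate of nearly 10% as it stands. That needs a rule that either endpoint counts, which the article never states, and near-independence, which is doubtful for endpoints taken from the same tests.
- A reader might count two exercise tests per period and infer four separate primary tests. The analysis section describes differences between periods and a regression that includes visit number. It does not declare a separate primary test at each visit.
- A reader might infer that RPP, listed first, is the natural gatekeeper. Nothing ranks it above ST depression. The only earlier RPP change quoted, "the rate pressure product at 0.1 mV STD (20500 ± 755 → 21907 ± 764 mmHg/min"), is 1407/20500 = 6.9%, against the 15% used for power.

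**Conclusion.** The point holds in conditional form. If either endpoint is enough, the familywise error is above the nominal 5%: up to 9.75% under independence and about 7–9.5% for correlations from 0.9 down to 0.3. If both are needed, the error is at most 5% and joint power is about 81% under independence. The correlations are assumptions, and the power figures assume exactly 90% per endpoint at 0.05, which the article does not allow one to check.

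This should be fixed. The documents do not show that the trial will use the inflated rule, only that they leave room for it.

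**What to change.** Before unblinding:

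1. In the data management and analysis section, replace the general threshold, for the two primaries, with one stated rule: Holm or Hochberg at a familywise two-sided 0.05; or a requirement that both be significant; or a fixed sequence with the order justified by the sponsor.
2. In the sample size section, name the endpoint and restate power for the chosen rule.
3. State that the secondary outcomes and the baseline-characteristic regressions are exploratory.

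The text changes are short, and the article reports recruitment still open in February 2015. The real cost is the power figure: about 83–84% for an endpoint tested at 0.025, or about 81% joint power under a both-required rule with independent endpoints. Keeping 26 patients means accepting that; restoring 90% at 0.025 would take about 31–32. A fixed sequence keeps the full 0.05 for the endpoint tested first, but makes the second conditional on it, which changes the standing of a declared primary after recruitment has begun and needs to be documented as such.

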## Discussion

The study will be conducted in compliance with the principles of the Declaration of Helsinki (2008), the principles of Good Clinical Practice and in accordance with all applicable requirements laid down by the Co-Sponsors of the study, namely: King’s College London and Guy’s and St Thomas’ NHS Foundation Trust. The trial protocol has received ethical approval from the National Research Ethics Service (NRES) Committee London – Westminster (Research Ethics Committee reference 11/LO/1564) of the United Kingdom. Annual progress and safety reports and a final report at conclusion of the study will be submitted to the Co-Sponsors and the Research Ethics Committee. The Medicines and Healthcare Products Regulatory Agency (MHRA) has also approved the study.

This trial has been funded by the British Heart Foundation via a Clinical Research Training Fellowship awarded to [name] (grant number FS/11/70/28917) and is supported by the Department of Health via the National Institute of Health Research comprehensive Biomedical Research Centre award to Guy’s and St Thomas’ NHS Foundation Trust in partnership with King’s College London and King’s College Hospital NHS Foundation Trust.

The LIONESS study is a single-centre trial based in the United Kingdom. The trial has, therefore, been registered with our national trials database via the National Institute of Health Research Clinical Research Network (NIHR CRN) portfolio (Study ID 11112) since May 4th 2012. The NIHR CRN trials database is accessible to the public at no charge, open to all prospective registrants, managed by a not-for-profit organization, has a mechanism to ensure the validity of the registration data, and is electronically searchable. The study has also been registered on ClinicalTrials.gov as of November 10th 2014 (NCT02315001). There have been minor amendments to the study protocol since first registration and as such the first patient was recruited in January 2014. The study remains actively recruiting as of February 2015.

It is intended that positive or negative study results will be reported and disseminated at international conferences and in an international peer-reviewed scientific journal.
